### Sample size calculation

Previous experience^34^ for studies of this type, where statistical models have been built to explain variation in PROMs, suggests that they rarely explain more than 10%–20% of the variation in outcomes (R^2^) at 12 months. Using a large (and therefore rather conservative) estimate for the numerator number of df of 25 (ie, the model complexity) for a putative F test of the model significance and an R^2^=0.1, suggests a sample size of 160 for 90% power at the 5% significance level (https://cran.r-project.org/web/packages/pwr/; pwr.f2.test).^35^ Experiences of previous such studies in similar settings have reported follow-up rates of 80%. Assuming lost to follow-up of 20%, 200 participants will be required for this study.

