## Discussion

This prospective cohort study aims to describe the baseline characteristics of young people (age <55) with a meniscal tear and to explore the relationship between these features at outcome. This study has a role in informing treatment decisions by identifying in certain patient features can predict treatment outcome. There is a view among researchers and clinicians that surgery may be beneficial among a particular subset of patients and further research is needed to identify this subset.^4^ This work will assist in the future planning of an RCT by further exploring the study population. The study aims to identify the patients that improve with both operative and non-operative management and whether there are certain factors which influence the response to either treatment. It may be that in a population of patients who do not improve with non-operative care and do not have features of arthritis, that a study is required to assess the effectiveness of surgery, but before this can be performed, we need a much better understanding of the characteristics of this population and how they might be defined. This cohort study will also inform a future trial by providing an insight into follow-up rates in this younger population, efficient means of collecting outcome data, and also providing an understanding of the MCID of the WOMET score.

This study aims to build on a previous cohort study which was performed in order to identify features which may predict variability in PROMs for patients following arthroscopy. The authors included 18 preoperative factors and found the strongest predictive factors were no previous meniscal surgery and more severe preoperative knee symptoms. However, factors such as tear pattern or structural OA were not assessed as preoperative imaging was not available to the authors, and so our study will answer a related, but different question. The models overall predictive performance was very low (optimum adjusted R^2^=0.080) suggesting the included factors had little relevance to outcome.^5^ The authors only included patients undergoing operative intervention, work is needed to identify outcomes in all patients that are managed with a meniscal tear, in order to identify which patients performed well with non-operative management and which perform poorly.

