An upper age limit of 55 was selected, as the mean age in a recent meta-analysis of trials in meniscal tears. As the one of the purposes of the study is to explore the relationship between baseline data and outcome, we will explore the effects on age. Age was not an important factor in the recently published analysis of the Knee Arthoscopy Cohort Southern Denmark (KACS) cohort and while it may be relevant, it may also be a poor proxy for other relevant factors, such as underlying OA or meniscal degeneration. This will be explored in this study and, if age is important, the study will allow us to set evidence-based thresholds for future research.

Strengths of the METRO cohort include its prospective nature, minimising the risk of participant recall bias. We are also reporting outcomes in all patients with a meniscal tear including both the operative and the non-operative group, this ensures the study results are more representative of all patients with a meniscal tear. The multicentre national nature of this study ensures that the data included are generalisable to current UK practice, especially after publication of the national treatment guidelines.^20^ Further strengths include the use of MRI based assessment of tear pattern, arthritis and bone shape change which could be an important predictive factor for outcome.

Limitation of this study design in comparison to previous research is our sample size is smaller than a previous study which did not identify any predictive factors,^5^ however, this study did not include MRI data and we have included a thorough sample size calculation with a conservative estimate of the number of df. In addition, this observational study will provide an insight into associations between patient factors and PROMs, however, as the study is observational the findings will be utilised for generation of new hypotheses and causal inference will be limited, and will require further study in RCTs. A multicentre RCT is currently recruitment comparing surgery versus physiotherapy, however, the eligibility criteria do not take into account presence of OA on MRI.^39^ This cohort study will explore whether that is an important factor in patient outcome.

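### The stated sample size of 160 for 90% power does not follow from its own inputs: they require 275 completers, and 160 gives 58% power

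*Protocol article*

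**What the plan says.** The Sample size calculation section of the protocol article gives a complete set of inputs. The calculation is "for a putative F test of the model significance". It uses a large "estimate for the numerator number of df of 25 (ie, the model complexity", and R² = 0.1. The section says of earlier models of this kind that "they rarely explain more than 10%–20% of the variation in outcomes", so R² = 0.1 is the lower end of the range it has in mind. It cites pwr.f2.test from the R package pwr and concludes that this "suggests a sample size of 160 for 90% power at the 5% significance level". Loss to follow-up is then added: "Assuming lost to follow-up of 20%, 200 participants will be required for this study".

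The Discussion comes back to the calculation. It concedes that the cohort is smaller than a previous study which found no predictive factors, and answers that "we have included a thorough sample size calculation with a conservative estimate of the number of df".

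**The concern.** Every input to the calculation is printed, so the figure can be checked without outside information. A 25-degree-of-freedom test of a model explaining only 10% of the variance spreads a small effect over many terms, and 160 looked too few for 90% power.

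Two things depend on this number. It is the only justification given for recruiting 200 people. It also tells readers how much weight a null result can bear: with 90% power, a model with a true R² of 0.1 would be missed one time in ten. If the real power is much lower, a non-significant model says far less about whether baseline and MRI features matter than the protocol implies. The authors intend the results to inform treatment decisions and the planning of a future trial.

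**Working it through.** **Inputs, all from the Sample size calculation section**
- Test: overall F test of the linear model
- Numerator degrees of freedom: u = 25
- R² = 0.1
- Significance level 0.05; power 0.90
- Function: pwr.f2.test
- Loss to follow-up: 20%

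**Formulae**
- f² = R² / (1 − R²)
- N = u + v + 1, where v is the denominator degrees of freedom
- Noncentrality λ = f² × (u + v + 1) = f² × N
- Power = P(noncentral F with u, v and λ exceeds the upper 5% point of the central F with u and v)

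**Attempt to reproduce 160**
1. f² = 0.1 / 0.9 = 0.1111.
2. Solving for 90% power with u = 25 gives v = 248.7, rounded up to 249.
3. N = 249 + 25 + 1 = 275. The plan states 160, which is 115 fewer.
4. Recruitment at 20% loss: 275 / 0.8 = 343.75, so 344. The plan states 200, which is 144 fewer. The plan's own inflation step, 160 / 0.8 = 200, is correct; it carries a wrong base figure forward.

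**Power at the stated size**
1. N = 160 gives v = 160 − 25 − 1 = 134.
2. λ = 0.1111 × 160 = 17.8, against 0.1111 × 275 = 30.6 at the size required.
3. Power = 58.0%. A simulation of 4,000 data sets with random predictors gave 58.3% at N = 160 and 89.2% at N = 275.
4. If all 200 were analysed (v = 174), power would be 72.7%.

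**Power at 160 completers and 25 degrees of freedom, by R²**

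| R² | Power |
|---|---|
| 0.10 (stated) | 58% |
| 0.15 | 84% |
| 0.168 | 90% |
| 0.20 | 96% |

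**Other readings tried**

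| Reading (25 df; other inputs as stated unless changed) | Result |
|---|---|
| f² entered directly as 0.1 | N = 303 |
| Power lowered to 80% | N = 226 |
| Significance level raised to 10% | N = 237 |
| 160 taken as v, so N = 186 | power 68.0% |
| λ = f² × (u + v) | v = 249.6; power at 160 is 57.7% |
| λ = f² × v | v = 272.9; power at 160 is 48.3% |
| R² = 0.15 | N = 181 |
| R² = 0.20 | N = 134 |
| f² = 0.2, that is R² = 0.2 / 1.2 = 0.167 | N = 162 |

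Of these, only f² = 0.2 comes near 160, and it contradicts the stated R². Keeping R² = 0.1 and cutting the model to 5 or 6 degrees of freedom also comes near (N = 154 and 164), but that contradicts the stated 25.

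**The case against.** The arithmetic is hard to dispute, so the case on the other side concerns what follows from it.

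- **The study is exploratory.** The article's aim is to describe and explore, its analysis section sets no decision rule on a global F test, and the Discussion says the findings will generate hypotheses. This stands as a limit on the consequences: no stated study decision turns on the F test, and nothing in the article says that a null model would be read as proof of no association. It does not make the stated 90% correct. The authors chose to justify the size by power, so the figure has to be right.
- **The slip may be in R², not in N.** If f² = 0.2 was entered, the 160 fits an R² of 0.167, which lies within the article's own 10% to 20% range, and the misprint is the R². This is possible, but the document cannot settle it. On either reading the inputs and the result contradict each other.
- **The word conservative is fairly used.** In both places it describes only the number of degrees of freedom, and a larger number does raise the required N. This stands; the word can stay. The claim to thoroughness in the Discussion is what the error undermines.
- **The previous cohort's adjusted R² of 0.080 is a poor guide.** That study covered operated patients only and had no imaging data. This is fair, and the conclusion here does not use it.

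**Conclusion.** The concern holds. With the inputs exactly as printed, the required number is 275 completers (344 recruited), not 160 (200 recruited). At 160 completers the power is 58% instead of 90%, so the chance of missing a true R² of 0.1 is about 42% instead of 10%.

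The conclusion rests on the stated inputs and on the standard noncentral F calculation that the cited function uses. It needs no outside figure. It is conditional on R² = 0.1 being the intended effect. If the authors meant an R² of about 0.17, the 160 is about right for 90% power, but the stated assumption is then wrong and considerably more optimistic than the one printed. The size is not poor across the whole range the article considers: power is 84% at R² = 0.15 and 96% at R² = 0.20.

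**What to change.** Keep 200 participants and correct the statement in the Sample size calculation section, for example: with 25 numerator degrees of freedom and a 5% significance level, 160 completers give 58% power for R² = 0.10 and 90% power for R² of about 0.17 or more. If the calculation was in fact run with a different effect size, state that value and the reason for it in place of R² = 0.1.

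In the Discussion, remove the description of the calculation as thorough, or replace it with the corrected power, so that the small sample is not defended by a figure that does not hold. The remark about the degrees of freedom can remain.

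The cost is a change of wording and a less favourable stated power. No further participants or data are needed. Should the authors wish to keep 90% power at R² = 0.1 with 25 degrees of freedom, the price is 344 recruited instead of 200.

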### Statistical analysis

Summary statistics will be used to describe baseline data. We will report means and SDs (95% CIs) for approximately normally distributed data and for other cases report the median and IQR. Mean 12 months PROMs scores will be reported for the whole cohort. We will also report mean 12 months PROMs for both the non-operative and operative group. Pearson correlation coefficients will be used to assess evidence for associations between baseline features and 12 months PROMs scores. A model will be developed relating the response variable (12 months PROM) to a number of explanatory variables (eg, data collected at baseline). The type and structure of the models used will depend on the distribution of the response variable, and the nature of the association between the response and explanatory variable. A linear model will be the initial choice in order to predict the response variable (12 months PROM) as a linear weighted sum of the explanatory variables. The ‘weights’ or parameters of this model are estimated using regression analysis; providing us with regression coefficients (parameter estimates), that characterise the association.

A sensitivity and specificity-based longitudinal anchor method will be used to calculate the minimum clinically important differene (MCID). The change in WOMET scores will be calculated for each group on the PGIC scale. This will be done by subtracting the 12-month WOMET from the baseline score. A mean change in WOMET score will be associated with each anchor on the PGIC as follows:

No change (or condition has got worse).Almost the same, hardly any change at all.A little better, but no noticeable change.Somewhat better, but the change has not made any real difference.Moderately better and slight but noticeable change.Better and a definite improvement that has made a real and worthwhile difference.A great deal better and a considerable improvement that has made all the difference.

We will then use the receiver operator characteristics (ROC) to determine the MCID with equal sensitivity and specificity to discriminate between the changed group^5–7^ and the unchanged group.^1–4^ The area under the ROC curve represents the probability the score discriminates between the unchanged and the changed group. A probability of >0.7 was deemed acceptable.

This methodology has been previously used in orthopaedic research and has been described in previous literature.^36 37^

Model fitting and analysis will be undertaken in R (R Core team (2013) R Foundation for statistical computing, Vienna, Austria).^38^

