**Methods and analysis:**

This is a multicentre prospective cohort study. Participants aged between 18 and 55 years with an MRI confirmed meniscal tear are eligible for inclusion. Baseline characteristics including age, body mass index, gender, PROMs duration of symptoms and MRI will be collected. The primary outcome measure is the Western Ontario Meniscal Evaluation Tool at 12 months. Secondary outcome measures will include PROMs such as EQ5D, Knee Injury and Osteoarthritis Outcome Score and patient global impression of change score at 3, 6 and 12 months.

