### Study aim

To describe the baseline characteristics and imaging findings of young patients with a meniscal tear and to explore the relationship, if any, between these baseline features and 12-month outcomes.

We will address the following research objectives:

Describe the baseline characteristics, pattern of symptoms and imaging findings of younger people (aged <55 years) with a meniscal tear (study population).Explore the relationship between these features and 12-month PROMS.

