### Baseline data collection

Once participants have provided informed consent, baseline data will be collected by the research team. Baseline characteristics such as age, gender, body mass index and date of potential injury and duration of symptoms will be collected. Baseline PROMs will be collected at recruitment in order to assess changes in PROMs at 12 months. Clinical features which are consistent with a treatable meniscal lesion, outlined by the BASK consensus meeting, will also be collected from the attending clinician (for a locked knee) and the participant (for locking and catching).^20^ These include the presence of:

Locked knee: sudden onset, complete mechanical block to flexion or extension of the knee, detected on clinical examination and which does not resolve despite adequate analgesia.Locking: an intermittent block to normal range of movement of the knee (commonly a block to extension) with an associated unlocking movement. Knee returns to near normal after unlocking.Catching: the sensation of something intermittently out of place in the knee and interfering with joint movement.

These will be assessed on initial baseline questionnaires which will be provided by the host site. If the clinician documents specific examination findings (in particular alignment), this will be collected by the study team.

MRI scans will be analysed to assess:

Anatomical location and tear pattern. Tear patterns include the following which have been recognised by BASK as potentially treatable ‘meniscal targets’.^20^
Bucket handle tear: a longitudinal tear involving more than 25% of the meniscus length (can be displaced or undisplaced).Displaced meniscal tear: fragments are displaced from their usual anatomical position.Meniscal root tear.Radial tear: a vertical tear which may or may not extend into the meniscocapsular junction.Horizontal tear.Complex tear: a meniscal lesion with more than one place of tear in continuity.Whole-Organ MRI Score (WORMS): This is a semiquantitative, multifeature scoring method for whole-organ evaluation of the knee using conventional MRI. It is based on 14 features include cartilage and meniscal integrity.^21^

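### The planned associations with 12-month scores do not commit to adjusting for the baseline score, so they cannot separate features that mark improvement from features that mark only severity at entry

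*Protocol article*

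**What the plan says.** All references are to the protocol article.

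- **Formal objective (Study aim).** Having described the baseline features, the study will "Explore the relationship between these features and 12-month PROMS". The primary outcome is WOMET at 12 months.
- **Feature-wise analysis (Statistical analysis).** "Pearson correlation coefficients will be used to assess evidence for associations between baseline features and 12 months PROMs scores". No adjustment is mentioned.
- **Model (Statistical analysis).** "A model will be developed relating the response variable (12 months PROM) to a number of explanatory variables (eg, data collected at baseline"). A linear form is the first choice. Baseline data appear only as an example of what may enter, and the baseline PROM is not named.
- **Why baseline PROMs are collected (Baseline data collection).** "Baseline PROMs will be collected at recruitment in order to assess changes in PROMs at 12 months".
- **Aim as worded in the Discussion.** "The study aims to identify the patients that improve with both operative and non-operative management". The same sentence adds an interest in what affects treatment response.

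The only analysis in which the text fixes a use for baseline WOMET is the MCID calculation, which takes the change from baseline to 12 months.

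**The concern.** The documents contain two questions. One is which features go with a better or worse score at 12 months. The other is which features go with improvement. An unadjusted correlation with the 12-month score answers the first question only.

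A feature such as locking, catching or a WORMS component may relate to WOMET at entry. If entry severity carries through to 12 months, that feature correlates with the 12-month score even when, among patients who start at the same level, it says nothing about how they do. Nothing in the Pearson coefficient reveals which case applies. The linear model would reveal it if the baseline score were a term, but whether it is one is left open.

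The Discussion expects the results to inform treatment decisions and to help define the population of a later randomised trial. For both uses, a marker of who improves and a marker of who started worse have different implications.

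**Working it through.** **Inputs from the protocol article**

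- Analysed sample: 160, from 200 recruited with 20% loss (160/0.8 = 200, which reproduces). The 160 is used here only as the planned number of completers. Whether it follows from its own power inputs is a separate matter.
- Significance level: 5%, taken as two-sided for the correlation test.
- Variance explained by whole models of 12-month PROMs: rarely above 10% to 20% (Sample size calculation).

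**Inputs assumed, because the document gives none**

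- Correlation of the feature with baseline WOMET, a: 0.3, with a range of 0.2 to 0.4.
- Correlation of baseline with 12-month WOMET, r: chosen so that baseline alone explains 10% to 20% of 12-month variance. Hence r = √0.10 = 0.316 to √0.20 = 0.447.

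**Step 1: the induced correlation.** If the feature is unrelated to the 12-month score once baseline is known, its unadjusted correlation with that score is a × r.

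- 0.3 × 0.316 = 0.095
- 0.3 × 0.447 = 0.134

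**Step 2: the chance of p<0.05 at n = 160.** By Fisher's z, z = atanh(a × r) × √(160 − 3), with √157 = 12.53. The chance is Φ(z − 1.96) + Φ(−z − 1.96).

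- r = 0.316: z = 1.19, so 0.221 + 0.001 = 0.22
- r = 0.447: z = 1.69, so 0.394 + 0.000 = 0.39

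**Step 3: range over the assumed feature–baseline correlation**

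| a | Baseline explains 10% | Baseline explains 20% |
|---|---|---|
| 0.2 | 12% | 20% |
| 0.3 | 22% | 39% |
| 0.4 | 36% | 62% |

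**Step 4: the same feature after adjustment.** The partial correlation given baseline is zero by construction, so the test should reject at its nominal level. Simulation of 20,000 cohorts of 160 for each of the six settings gave 4.7% to 5.2%. The unadjusted rates in the same runs were 12% to 62%, in agreement with the table.

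**Step 5: would correlating with change scores do instead?** No. With equal SDs at both times, the same feature has correlation −a × √((1 − r)/2) with the change. For a = 0.3 and r = 0.316 this is −0.3 × √0.342 = −0.175, which is larger in size than the 0.095 in Step 1. Change scores pick up the baseline relation with the opposite sign. Only conditioning on baseline removes it.

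**The case against.** **The objective is association with 12-month PROMs, and that is what is tested.** This stands. For status at 12 months the Pearson coefficients are valid description. A feature that marks persistent severity truly is associated with the 12-month score, so the 22% to 39% is not a false-positive rate for that question. It is the rate at which such a feature would show an association that says nothing about improvement.

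**A reader might infer that the plan will declare predictors of who improves from these correlations.** The document does not support that. It sets no selection or declaration rule, and the Discussion says the findings are for generating hypotheses, with causal inference limited.

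**The multivariable model can hold the baseline score.** It can. PROMs are listed among the baseline characteristics in the Abstract and are collected under Baseline data collection. So the model does not exclude the baseline score, but it does not commit to it either.

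**A covariate list belongs in a fuller document.** That is fair for the full list. The point here is narrower: the article fixes the unadjusted analysis as its feature-wise way to assess evidence, and leaves open the one covariate that decides whether a coefficient speaks to improvement.

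**Higher persistence would give larger figures.** A reader might take a baseline-to-12-month correlation of 0.5, which with a = 0.3 gives about 47%. But 0.5 means that baseline alone explains 25% of the variance, above what the article expects of whole models, so figures of that size are not supported. Even the 10% to 20% used here gives baseline alone the share that the article gives to a whole model. If baseline explains less, the rate falls towards 5%.

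**Conclusion.** The point holds in a limited form. The planned analyses are sound for unadjusted association with 12-month status. As written they cannot tell a marker of improvement from a marker of severity at entry, although the article names improvement as an aim and change as the reason for collecting baseline PROMs.

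The size is illustrative: about 22% to 39% unadjusted against about 5% adjusted. It rests on an assumed feature–baseline correlation of 0.3, on baseline explaining 10% to 20% of 12-month variance, on 160 completers, and on a feature with no relation to outcome given baseline. Over feature–baseline correlations of 0.2 to 0.4 the range is 12% to 62%. The direction of the problem does not depend on these values, but its size does. The change is worth making because the data are already being collected.

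**What to change.** In the Statistical analysis section:

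1. State that the baseline value of the same PROM is always a term in the model of the 12-month score, for WOMET, KOOS4 and EQ-5D. All three are collected at baseline.
2. Report each feature-wise association from a regression of the 12-month score on the feature plus that baseline value, or equivalently as a partial correlation.
3. Keep the unadjusted Pearson coefficients, labelled as descriptive of 12-month status only.

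Do not replace the 12-month score by the change score without baseline in the model, for the reason in Step 5 of the working.

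The cost is one degree of freedom per model, small against the 25 allowed for in the sample size calculation, and a rule for missing baseline scores. These should be few, because baseline PROMs are collected at recruitment. No new data are needed.

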A well-designed cohort study needs to be performed with patients being recruited at the point of diagnosis or presentation to an orthopaedic specialist. This will allow researchers to include patients being managed non-operatively. By including MRI analysis in a potential predictive model, this will produce a comprehensive model to identify which features can predict variability in patient-reported outcome measures (PROMs).

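### At the sample size section's own inputs (up to 25 df, 160 analysed, R² = 0.1), a linear prediction model fitted by ordinary least squares would be heavily overfitted; report optimism-corrected performance and fix the predictors in advance

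*Protocol article*

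**What the plan says.** The Introduction sets a predictive goal for a cohort study with MRI data: "this will produce a comprehensive model to identify which features can predict variability in patient-reported outcome measures". The Statistical analysis section then states the method: "A linear model will be the initial choice in order to predict the response variable (12 months PROM) as a linear weighted sum". The coefficients come from regression analysis; no penalty or shrinkage is named, so ordinary least squares (OLS) is the plain reading. The same section correlates baseline features with 12-month scores by Pearson coefficients and leaves the form of the model open: "The type and structure of the models used will depend on the distribution of the response variable, and the nature of the association".

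The Sample size calculation gives the planned scale. On model size: "Using a large (and therefore rather conservative) estimate for the numerator number of df of 25", which the article equates with model complexity. On effect and number: "an R^2^=0.1, suggests a sample size of 160 for 90% power at the 5% significance level". On what earlier work found: "they rarely explain more than 10%–20% of the variation in outcomes (R^2^) at 12 months". On attrition: "Assuming lost to follow-up of 20%, 200 participants will be required for this study".

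The Discussion gives the study a role in guiding treatment choice and in planning a randomised trial. It also describes the findings as hypothesis-generating. It quotes an earlier cohort's model, with 18 factors, as reaching an adjusted R² of 0.080.

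**The concern.** Twenty-five df in 160 patients is 160/25 = 6.4 patients per parameter, with a signal expected to be weak. Least squares then fits a good deal of noise. Two things follow. Raw R² in the study's own data looks much better than the model deserves. The coefficients are also too extreme as a set, so predicted scores for new patients are too spread out.

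Calling 25 df conservative is right for the power of an F test, where more df means a larger required sample. It gives no protection against overfitting, where more df makes matters worse.

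This matters to the extent that the fitted model is used for prediction: to say how well baseline and MRI features forecast outcome, to inform treatment, or to define the population of the next trial. It matters much less if the coefficients are read only as associations with confidence intervals.

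**Working it through.** **Inputs.** From the Sample size calculation: p = 25 df, n = 160 analysed, true R² = 0.1, prior range 0.10 to 0.20, 20% loss. From the Discussion: adjusted R² of 0.080 in the earlier cohort. Assumed here: OLS, the model fixed in advance, and roughly normal predictors.

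**1. The plan's own figures.** The step 160/(1 − 0.20) = 200 reproduces. The 160 does not. With f² = 0.1/0.9 = 0.111, 25 numerator df, 5% significance and 90% power, the noncentral F calculation gives 248.7 denominator df and N = 275. Power at N = 160 is 58%. That is a separate point; 160 is used below because it is the number the article plans to analyse.

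**2. Raw R² with no signal.** The expected value is p/(n − 1) = 25/159 = 0.157. The 95th percentile is 0.229.

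**3. Raw R² at true R² = 0.10.** Approximately 1 − (1 − R²)(n − p − 1)/(n − 1) = 1 − 0.9 × 134/159 = 0.24.

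**4. Prediction error in new patients.** As a fraction of the outcome variance:
- Model: (1 − R²)(n + 1)(n − 2)/[n(n − p − 2)] = 0.9 × 161 × 158/(160 × 133) = 1.076.
- Cohort mean: 1 + 1/n = 1.006.
- Out-of-sample R² against the cohort mean: 1 − 1.076/1.006. The (n + 1)/n terms cancel, which leaves 1 − (1 − R²)(n − 2)/(n − p − 2) = 1 − 0.9 × 158/133 = −0.069.

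**5. Sensitivity, same formula.**

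| n | df | true R² | out-of-sample R² |
|---|---|---|---|
| 160 | 25 | 0.08 | −0.093 |
| 160 | 25 | 0.10 | −0.069 |
| 160 | 25 | 0.15 | −0.010 |
| 160 | 25 | 0.20 | +0.050 |
| 160 | 15 | 0.10 | +0.006 |
| 160 | 5 | 0.10 | +0.071 |
| 200 | 25 | 0.10 | −0.030 |

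Setting the formula to zero gives break-even at R² = p/(n − 2). For n = 160 and 25 df that is 25/158 = 0.158. For R² = 0.1 and n = 160 it is 0.1 × 158 = 15.8, so at most 15 df. For R² = 0.1 and 25 df it is n = 25/0.1 + 2 = 252.

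**6. Spread of the predictions.** With outcome variance 1, the signal variance is 0.1, and estimation noise adds 25 × 0.9/133 = 0.169 to the variance of the predicted scores. The calibration slope is then about 0.1/(0.1 + 0.169) = 0.37, so differences between predicted scores are more than twice too large.

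**7. Simulation.** 3,000 datasets per scenario, n = 160, 25 independent normal predictors.
- No signal: mean raw R² 0.158, adjusted R² 0.001.
- True R² = 0.10: raw 0.239, adjusted 0.098, out-of-sample −0.071; worse than the mean in 93% of datasets.
- True R² = 0.20: out-of-sample +0.050; worse than the mean in 14%.

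Treating the predictor values as fixed points the same way: 0.9 × (1 + 26/160) = 1.046 against 1.006.

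**The case against.** **The plan does not commit to 25 df.** This stands. The figure is an upper planning value for a notional F test, and no predictor list is given. A reader might infer that the planned model must predict worse than the cohort mean. The documents do not support that: at R² = 0.1 a prespecified model of 15 df or fewer does at least as well as the mean, and at R² = 0.20 even 25 df does slightly better.

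**The plan does not say that it will judge the model by raw R².** This also stands. A reader might take the 10% to 20% range as a standard that pure noise could meet, since 0.157 lies inside it. The article gives that range as prior experience behind the assumed effect and names no performance measure for its own model. The F test allows for df. The one performance figure it quotes from earlier work is an adjusted R², which the simulation shows to be nearly unbiased here. The 0.157 misleads only if raw R² is reported without correction.

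**The plan does not say that the Pearson correlations select predictors.** A reader might infer screening, because model structure is to depend on the nature of the association. That wording may equally mean functional form. No selection rule is stated, so no false-positive rate can be attached to one.

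**Validation or shrinkage may sit in an analysis plan that is not shown.** That is possible, and its absence from an article is not the point made here. The point is that the method and scale the article does state would, if followed as they read, give an overfitted predictor.

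**The aim is exploratory.** In part. The Study aim concerns relationships, and OLS with intervals suits that. But the Introduction and Discussion also speak of prediction and treatment decisions, and the overfitting bears on those uses.

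**Conclusion.** The concern holds in a limited form. At the article's planning inputs, an OLS fit would show a raw R² of about 0.16 with no signal and about 0.24 when the true value is 0.10. In the latter case its out-of-sample R² against the cohort mean would be about −0.07. These figures assume OLS, the full 25 df, a model fixed in advance and roughly normal predictors. The deficit disappears at about 15 df for R² = 0.1, or at a true R² of about 0.158 with 25 df, and it falls to −0.03 if all 200 recruited patients are analysed.

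The overall F test and adjusted R² remain valid for a prespecified model, so the significance test itself is not in question. What needs protection is any statement about predictive performance and any predictive use of the coefficients.

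**What to change.** - List the candidate predictors, and the df each will use, before 12-month outcomes are examined. The break-even figures above show what each df costs.
- State that the Pearson correlations are descriptive and do not select predictors.
- Keep OLS coefficients with confidence intervals for describing associations.
- Report adjusted R² and bootstrap optimism-corrected R², with every modelling step repeated in each resample, together with a calibration slope.
- Apply the bootstrap shrinkage factor to any coefficients used for prediction.

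Ridge or lasso is optional: it would also reduce overfitting, but it biases coefficients toward zero and gives less simple intervals, a real trade-off for a study of associations. The cost of the changes is a little more R code and a lower reported R². No further patients or data are needed.
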